## Abstract

**Background:**

Approximately 17 % of all fractures involve the distal radius. Two-thirds require reduction due to displacement. High redislocation rates and functional disability remain a significant problem after non-operative treatment, with up to 30 % of patients suffering long-term functional restrictions. Whether operative correction is superior to non-operative treatment with respect to functional outcome has not unequivocally been confirmed. The IlluminOss® System was introduced in 2009 as a novel, patient-specific, and minimally invasive intramedullary fracture fixation. This minimally invasive technique has a much lower risk of iatrogenic soft tissue complications. Because IlluminOss® allows for early mobilization, it may theoretically lead to earlier functional recovery and ADL independence than non-operative immobilization. The main aim of this study is to examine outcome in elderly patients who sustained a unilateral, displaced, extra-articular distal radius fracture that was treated with IlluminOss®.

**Methods/design:**

The design of the study will be a multicenter, prospective, observational study (case series). The study population comprises elderly (60 years or older; independent in activities of daily living) with a unilateral, displaced, extra-articular distal radius fracture (AO/OTA type 23-A2 and A3) that after successful closed reduction was fixed within 2 weeks after the injury with IlluminOss®. Critical elements of treatment will be registered, and outcome will be monitored until 1 year after surgery. The Disabilities of the Arm, Shoulder, and Hand score will serve as primary outcome measure. The Patient-Rated Wrist Evaluation score, level of pain, health-related quality of life (Short Form-36 and EuroQoL-5D), time to ADL independence, time to activities/work resumption, range of motion of the wrist, radiological outcome, and complications are secondary outcome measures. Health care consumption and lost productivity will be used for a cost analysis. The cost analysis will be performed from a societal perspective. Descriptive data will be reported.

**Discussion:**

The results of this study will provide evidence on the effectiveness of operative treatment of patients who sustained an extra-articular distal radius fracture with the IlluminOss® System, using clinical, patient-reported, and societal outcomes.

**Trial registration:**

The study is registered at the Netherlands Trial Register (NTR5457; 29-sep-2015).

## Background

Distal radius fractures are the second most common osteoporotic fractures [1]. The number of hospitalizations due to these fractures in The Netherlands in patients aged 50 years and older increased from 877 in 1997 to 2912 in 2009 [2]. In line with demographic developments, osteoporotic fractures including those of the wrist can be expected to increase further in the coming years, with a concomitant increased burden on health care resources [3–5].

The current standard treatment for patients with a displaced extra-articular distal radius fracture as mentioned in the Dutch treatment guideline is closed reduction and plaster cast immobilization for 4–6 weeks [6]. Non-operative treatment remains controversial due to high dislocation rates (36–57 %) and often disappointing functional recovery [6–11]. Immobilization may also induce stiffness. Multiple studies have shown that comminuted extra-articular distal radius fractures are characterized by instability, and plaster immobilization will usually not prevent substantial redisplacement [8, 12, 13].

Several operative procedures are used for extra-articular distal radius fractures. In osteoporotic bone, angular stable plates are widely used, whereas the interest in and use of intramedullary devices is growing. Potential advantages of modern intramedullary devices could be the minimal surgical exposure for introduction of the device and the low risk of implant-related soft tissue irritation. This includes a reduced risk of tendon injury and screw penetration into the joint, which are the main problems of volar plating [14]. A recent literature review showed that intramedullary nailing gives a comparable range of motion, functional outcome, and grip strength as other fixation techniques, however the 0–50 % complication rate may raise concerns about the role of intramedullary nailing [15]. In addition to injury of the superficial radial nerve as most common complication (occurring in 9.5 % of patients), irritation from metalwork, tenosynovitis, and infection occurred in 1-2 % of patients. New devices and surgical techniques should be aimed at reducing the risk of these complications.

The llluminOss® System is the first percutaneous, patient-specific, fracture stabilization system [16]. Only a small and percutaneous incision is required to insert an inflatable balloon into the medullary canal. The balloon, which spans the fracture is infused with a light curable monomer. The monomer hardens in situ by applying a visible light, resulting in a stable and patient-specific implant that provides longitudinal strength and rotational stability over the length of the implant. Early functional after-treatment without additional plaster immobilization is possible. The latter is considered the main strength of this device over non-operative treatment and conventional metal implants [16].

The IO-WRIST study is designed to determine results after treatment with IlluminOss®. Outcome will be monitored as propagated by the distal radius working groups of the International Society for Fracture Repair and the International Osteoporosis Foundation [17]. This study primarily aims to examine the effect of operative treatment using the IlluminOss® System on the DASH (Disabilities of the Arm, Shoulder, and Hand) score in elderly patients who sustained a unilateral, displaced, extra-articular distal radius fracture. Secondary objectives are to examine the effect on functional outcome, the level of pain, health-related quality of life, the time to regaining independence in activities of daily living (ADL), the resumption of work/ADL, range of motion of the wrist, the time to radiographic healing, the rate of complications with associated secondary interventions, and the costs for health care use and lost productivity.

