## Methods/design

### Study design

The IO-Wrist study is a multicenter, prospective, observational study (i.e., case series). As the intervention studied is a relatively new technique and there is a lack of published evidence a case series was preferred over a study comparing the intervention with a control group. The following four hospitals in The Netherlands will participate: 1) Albert Schweitzer Hospital, Dordrecht; 2) Amphia Hospital, Breda; 3) Deventer Hospital, Deventer; and 4) Erasmus MC, Rotterdam. The study is registered at the Netherlands Trial Register (NTR5457), registration date September 29, 2015.

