### Study population

All elderly persons aged 60 years or older, who were independent in activities of daily living before the injury, presenting to the ED with a unilateral, displaced, extra-articular distal radius fracture (AO/OTA type 23-A2 and A3) [18] and treated with IlluminOss® will be considered eligible for inclusion. The fracture will be classified on lateral (preferably lateral carporadial) and anteroposterior (AP) radiographs.

The inclusion criteria are:Adult men or women with an age of 60 years or olderA unilateral, displaced, extra-articular distal radius fracture (AO/OTA type 23-A2 or A3), as confirmed on X-ray (lateral (preferably lateral carporadial) and AP)Capable of independent activities of daily living prior to index injury*Closed reduction and intramedullary fixation using the IlluminOss® System within 14 days after traumaProvision of informed consent by patient.

* This will be assessed using a simple yes/no question concerning their independence.

The exclusion criteria are:Additional traumatic injuries if this affects treatment, rehabilitation, or function of the affected wristA pathological, recurrent, or open (i.e., Gustilo-Anderson grade II or III) fractureAn impaired wrist function at the affected side) due to arthrosis, rheumatoid disorder, or neurological disorder prior to the injuryA bone disorder (excluding osteoporosis), that may impair bone healing (e.g., osteomalacia, renal osteodystrophy, or Paget’s disease)Patient is unwilling or unable to comply with the after-care protocol and follow-up visit scheduleInsufficient understanding of the Dutch language for adequate comprehension of the treatment information or rehabilitation program, as judged by the attending physician or researcherParticipation in another surgical intervention or drug study.

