### Sample size calculation

For case series, a generally accepted assumption is that introducing and implementing a (relatively new) surgical technique requires 30 patients [39]. A formal sample size calculation for this study is based on the DASH score (primary outcome measure). The minimal important change for the DASH score is 10 points [19]. Based on literature data we expect a mean DASH of 23 (SD 19) in non-operatively treated patients [40, 41]. In order to detect a 10-point improvement (mean 13, SD 10) in patients treated with IlluminOss® with a two-sided α of 0.05 and a 90 % power (β = 0.10), at least 38 patients are needed. Anticipating 10–15 % loss to FU and 10 % mortality, 50 patients will be enrolled.

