## Discussion

Despite the frequent occurrence of distal radius fractures, treatment is still at debate. The ultimate goal of treating a distal radius fracture is to restore full wrist function as early as possible. Full range of motion in the wrist declines with disuse and the introduction of early motion following a fracture is critical for the early restoration of normal function, but also for regaining ADL independence. Especially the latter is considered the main strength of the IlluminOss® System. The IO-Wrist study is aimed at determining the effect of operative treatment of distal radius fractures using the IlluminOss® System. Treating patients with this device is expected to result in good and fast functional recovery (i.e., low DASH and high PRWE scores). When comparing outcome with published data on non-operative treatment (i.e., closed reduction and 4–6 weeks plaster cast immobilization, with surgical intervention only if secondary dislocation occurs), we expect similar outcome at 1 year post-injury. However, improved DASH scores are expected to be noticeable until 6 months after treatment initiation, reflecting faster functional recovery in the operative group. Patients operated with IlluminOss® are expected to regain independence sooner and therefore to consume less health care. Improved recovery as well as less total health care use would justify higher costs for the initial surgery. As far as we know, this is the first high-quality study that will evaluate outcome after treating patients with an extra-articular distal radius fracture operated with the IlluminOss® System, using patient-reported, clinical, and economic outcomes.

Four hospitals in the Netherlands participate in this study. The first patient was included on August 31, 2015. Inclusion is expected to be completed within a year. With a follow-up of 1 year data presentation is expected by the end of 2017.

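### The objectives and the promised contribution speak of an effect and effectiveness, but the design is a single-arm case series that can only describe outcome

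*Protocol article*

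**What the plan says.** The protocol article states its purpose in two ways.

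**Causal wording.** The Background section gives the primary objective: "This study primarily aims to examine the effect of operative treatment using the IlluminOss® System on the DASH". The secondary objectives there are also framed as effects. The Discussion restates the aim: "The IO-Wrist study is aimed at determining the effect of operative treatment of distal radius fractures using the IlluminOss® System". The Discussion paragraph of the abstract describes the contribution: "The results of this study will provide evidence on the effectiveness of operative treatment of patients".

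**Descriptive wording and design.** The Background paragraph of the abstract says: "The main aim of this study is to examine outcome in elderly patients". The abstract's methods paragraph announces descriptive reporting. The Study design section explains that "a case series was preferred over a study comparing the intervention with a control group", because the technique is new and published evidence is scarce.

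**The reference.** Under Sample size calculation the article says: "Based on literature data we expect a mean DASH of 23 (SD 19) in non-operatively treated patients". It then powers the study for a 10-point improvement, to a mean of 13 (SD 10). The Discussion foresees a comparison with published non-operative results. It expects better DASH scores up to 6 months and similar scores at 1 year.

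**The analysis.** The Statistical analysis section plans descriptive summaries, a Wilcoxon signed rank test of 1-year scores against the first measurement, and regression models within the treated cohort.

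**The concern.** An effect of a treatment on DASH is a contrast with what the same patients would have scored under another treatment. This study observes only treated patients, so the other side of the contrast has to come from the literature.

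That reference is described by its treatment, but not by age, fracture type, pre-injury function or time point. The cohort is selected on several of these. Patients must be 60 or older with a displaced AO/OTA A2 or A3 fracture. They must also meet the criterion "Capable of independent activities of daily living prior to index injury", have no prior impairment of the affected wrist and be able to follow the after-care. They must have been successfully reduced and operated on within 14 days, and they may be included as late as the 2-week visit. Any gap between the cohort and the published mean therefore mixes device, selection and timing.

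At stake is what the study may conclude. The article goes on to argue that better recovery and lower care use would justify the cost of surgery, so a comparative reading of the results is foreseen.

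**Working it through.** **1. The stated sample size.** Inputs from Sample size calculation: difference 10, reference SD 19, IlluminOss SD 10, two-sided alpha 0.05 (z = 1.960), power 90% (z = 1.282).

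- One sample against a known constant, SD 19: n = (19 × (1.960 + 1.282) / 10)² = 37.93, so 38. This is the stated figure.
- One sample, SD 10: (10 × 3.242 / 10)² = 10.5, so 11.
- Two groups, SDs 19 and 10: (361 + 100) × 3.242² / 100 = 48.4, so 49 per arm.

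At 80% power the two-group formula gives 461 × (1.960 + 0.842)² / 100 = 36.2, so 37 per arm, which is near 38. But 80% is not the stated power, and there is no second arm. At the stated power, 38 fits a contrast with 23 treated as known without error.

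**2. Does the planned analysis supply a valid contrast?**

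- The Statistical analysis section lists no test against 23 and no matching or adjustment to published data.
- Its regression models relate covariates to outcome among treated patients only.
- Its one named outcome comparison is 1 year versus first measurement. Table 1 puts the first DASH at 2 weeks after surgery, so the change includes natural healing and starts after the treatment was given.

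None of these identifies a treatment effect.

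**3. How much could selection matter? (Illustration.)** Assume that the device has no effect, that the cohort's expected DASH is b points below 23 because of who is included, that the SD is 19, and that n = 38. A two-sided one-sample t test rejects when |t| > 2.026 (37 df). The noncentrality is b × √38 / 19 = b / 3.082.

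| b (points) | Noncentrality | Chance of a significant difference from 23 |
|---|---|---|
| 2 | 0.649 | 9.7% |
| 3 | 0.973 | 15.8% |
| 5 | 1.622 | 35.2% |

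Five points is half the stated minimal important change of 10. The value of b is assumed and no figure in the article supplies it. If selection raised DASH by b instead, the same percentages would apply in the other direction.

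**4. What the design can deliver.** The 95% confidence interval half-width for mean DASH at n = 38 is 2.026 × SD / √38:

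- SD 10: 2.026 × 1.622 = 3.3 points.
- SD 19: 2.026 × 3.082 = 6.2 points.

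**The case against.** The strongest reply is that this is loose wording. The design is openly called a case series, the absence of controls is justified, the abstract is descriptive, and the analysis section is mostly descriptive too. That is largely right. The choice of a case series is not the fault, and a reader is not misled about the design. But the causal wording appears in the primary objective, the secondary objectives, the Discussion and the promised contribution. It is backed by a sample size for a between-treatment difference and by a foreseen literature comparison, so it is more than a slip in one sentence.

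Four stronger readings are tempting, and the article does not support them.

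- *The benchmark is unrestricted.* The cited sources are not available here, so their populations are unknown. The Discussion also narrows the published comparator to reduction and cast, with surgery only for redisplacement. One can say only that the reference is not described as matching the entry criteria.
- *The study will report any mean below 23 as a device effect.* No test against 23 and no decision rule is listed. The value appears only in the sample size rationale.
- *Selection must favour lower DASH.* Independence and compliance may point that way. Older age and displaced, possibly unstable fractures may point the other way. The net direction is unknown.
- *The false-positive rate could reach 85%.* A 5-point difference with SD 10 does give that figure. But the article projects SD 10 together with a device benefit, so using it under no effect needs a further assumption.

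**Conclusion.** The concern holds as a mismatch between claim and design. The objectives and the stated contribution name an effect and effectiveness, while the design, the abstract's aim and the listed analyses support description only. A difference from published non-operative results, in either direction, cannot be attributed to the device.

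The possible size can only be illustrated. The figures of about 10%, 16% and 35% rest on an assumed selection difference of 2, 3 or 5 points, SD 19, 38 evaluable patients, and a test that the article does not list. They are not error rates of the planned analysis. The conclusion rests on the design and the wording, and does not depend on these figures. The point is worth acting on because it changes what the study may conclude.

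**What to change.** 1. In the Discussion paragraph of the abstract, the primary and secondary objectives in the Background, and the aim in the Discussion, replace the effect and effectiveness wording with the abstract's own aim: to describe DASH and the other outcomes after IlluminOss fixation, per visit, with 95% confidence intervals. With 38 evaluable patients the expected half-width for mean DASH is about 3.3 to 6.2 points (SD 10 to 19).
2. State that no treatment effect will be concluded.
3. Label the comparison with published non-operative data exploratory and unadjusted. Take the reference at the same time point and from patients as close to the entry criteria as the sources allow. Report how large a selection difference would remove any observed gap.

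The cost is rewording and a more careful choice of published reference data. The study gives up an effectiveness claim that its design cannot support. It needs no additional patients or measurements.

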## Methods/design

### Study design

The IO-Wrist study is a multicenter, prospective, observational study (i.e., case series). As the intervention studied is a relatively new technique and there is a lack of published evidence a case series was preferred over a study comparing the intervention with a control group. The following four hospitals in The Netherlands will participate: 1) Albert Schweitzer Hospital, Dordrecht; 2) Amphia Hospital, Breda; 3) Deventer Hospital, Deventer; and 4) Erasmus MC, Rotterdam. The study is registered at the Netherlands Trial Register (NTR5457), registration date September 29, 2015.

### Recruitment and consent

Eligible persons who present to the Emergency Department (ED) with a unilateral, displaced, extra-articular distal radius fracture will be informed about the study after the fracture has been reduced or as early as possible after operative treatment. They may receive the information at the ED or upon admission at the surgical ward. The clinical investigator, an assistant, or the attending physician will explain the study, and give the patient written information and a consent form. Patients meeting all eligibility criteria will be included as soon as possible. This can be done while patients are still at the ED or when they return to the outpatient department at 2 weeks after surgery.

In order to reduce bias as much as possible, the follow-up measurements by the clinical investigator or research assistant will be performed using a standardized protocol. Evaluation of fracture healing from radiographs will be done by two (independent) trauma surgeons independently. Any disagreement will be discussed and until consensus is reached.

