Radiographic evaluation will be done using routinely obtained radiographs. The degree of radial inclination, volar/dorsal tilt and ulnar variance, the amount of comminution, and the radial length will be measured directly in the digital Picture Archiving and Communication System (PACS) of the participating hospital on standard AP, lateral carporadial, or lateral wrist X-rays. Radiographs will be made using a standardized protocol; 1) for the AP radiographs, the shoulder should be held in 90° abduction, the elbow in 90° flexion, and the wrist in neutral position; 2) for the lateral X-rays, the shoulder should be held in a neutral position and the elbow in 90° flexion; 3) for the lateral carporadial radiographs, the lower arm should be positioned on a 20–25° angled wedge.

Radiographic healing and alignment of the distal radius will be evaluated using X-rays. The treating physician and two independent experts will assess the Lidström score for the repeated X-rays of the wrist blinded from the first assessment [36]. X-rays will be blinded and radiographic evaluation will be done by two experts independently. Any discrepancy will be resolved in a consensus meeting.

The following complications will be collected from the patients’ hospital records; 1) skin problems (threatened skin, necrosis); 2) Surgical site infection [37]; 3) radial nerve pathology; 4) vascular injury (hemorrhage, injury to the radial or ulna artery); 5) tendon pathology (abductor pollicis brevis/longus, extensor carpi radialis brevis/longus, extensor pollicis longus); 6) compartment syndrome; 7) secondary dislocation (loss of length, angulation, or rotation); 8) implant failure (balloon breakage); 9) non-union/pseudarthrosis (i.e., no healing or progress towards healing visible at 6 months after surgery); 10) malalignment severe enough to treat surgically; 11) CRPS type I; 12) systemic, generic or other complications.

Secondary intervention within 1 year of surgery will be collected from the patients’ hospital records. Only interventions aimed at relieving pain, treating infection, promoting fracture healing, or improving function will be recorded. They will be categorized as 1) drug treatment (oral or intraveneous antibiotics, other); 2) surgical treatment (incision and drainage, revision osteosynthesis (plate osteosynthesis, intramedullary nail or other), implant removal, other).

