A custom-made questionnaire will be designed to collect details of health care consumption and work absenteeism (i.e., production loss). Health care use associated with diagnosis, treatment, and rehabilitation will be collected. This includes medical specialist care, hospitalization, medication, nursing care, physical therapy, and general practice care [21].

The following data will be collected in order to describe the population and intervention:Patient characteristics: age, gender, American Society of Anesthesiologists’ (ASA) classification, tobacco use, comorbidities, medication use, dominant side, sports activities prior to injury, work prior to injury, household composition, and ADL pre-injury.Injury characteristics: mechanism of injury, affected side, AO fracture classification [38], and additional injuries.Intervention characteristics: time between injury and surgery, length and diameter of PET balloon used, duration of surgery, peroperative complications, admission duration at the Intensive Care Unit and in hospital, type and duration of immobilization (including the use of a sling or collar and cuff), time between trauma and the first physical therapy session, and the duration of physical therapy *(*i.e., total number of sessions).

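### Entry may be settled up to the 2-week visit and depends on having had IlluminOss fixation, so converted attempts fall outside the cohort and early failures may be missed; complication rates can be biased in the device's favour

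*Protocol article*

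**What the plan says.** Three parts of the protocol article together decide who enters the cohort.

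- **Timing.** Under Recruitment and consent, eligible persons will be "informed about the study after the fracture has been reduced or as early as possible after operative treatment". On inclusion, the same section continues: "This can be done while patients are still at the ED or when they return to the outpatient department at 2 weeks after surgery". The sentence before that asks for inclusion as early as possible. Table 1 gives the 2-week visit a window of 10 to 16 days after surgery.
- **Treatment received.** Under Study population, those otherwise suitable "and treated with IlluminOss® will be considered eligible for inclusion". The inclusion list repeats the condition, as closed reduction and IlluminOss fixation within 14 days of trauma. The abstract describes a fracture "that after successful closed reduction was fixed within 2 weeks after the injury with IlluminOss".
- **Compliance.** The exclusion list removes patients who will not or cannot follow the after-care and visit schedule. The text does not tie this judgement to information available before surgery.

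The Background makes "the rate of complications with associated secondary interventions" a secondary objective. Under Outcome measures, the listed complications include balloon breakage as implant failure, and "peroperative complications" are recorded as an intervention characteristic.

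**The concern.** A case series of a new device is informative about safety only if its denominator is everyone in whom the device was tried. Here entry depends on the treatment actually received, and it may be settled after the early result is known.

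This matters more than usual for two reasons. There is no concurrent control group in which the same selection would operate. And the Discussion intends to set the results beside published non-operative treatment, described there as including surgery when secondary dislocation occurs. A comparator described in that way keeps its early failures, whereas the IlluminOss cohort may lose some of its own. The Background also presents complications as the open question for intramedullary fixation, citing a range of 0 to 50%.

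**Working it through.** **1. Which cases can be lost, and how**

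| Course of the patient | Meets the entry criteria as written? | Can be missing from the cohort? |
|---|---|---|
| Attempt abandoned or converted, no IlluminOss fixation | No, on the wording of Study population and the abstract | Yes, by rule, even with consent before surgery |
| Fixation done, then redisplacement, revision or severe complication before the 2-week visit | Yes | Possible: not approached, declines, or judged unable to comply |
| Fixation done, intra-operative or early complication, enrolled | Yes | No; the event is taken from hospital records |

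Any bias therefore comes from who enters, not from poor recording among those who do.

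**2. The plan's own figure**

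The sample size supplies only the denominator of 50. With SD 19, a difference of 10, two-sided α 0.05 and 90% power, n = (19 × (1.960 + 1.282) / 10)² = 37.9, so 38, as stated. Allowing for 15% loss to follow-up and 10% mortality, 38 / (0.85 × 0.90) = 49.7, so 50. Nothing in the present point depends on this calculation, and the plan gives no figure for failed attempts or early failures.

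**3. Illustration for complications**

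Let x be the complications seen among 50 enrolled patients and k the failures not enrolled, each counted as one complication. The rate over all attempts is (x + k) / (50 + k). Both x and k are assumptions.

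| k omitted | x = 0 (reported 0%) | x = 5 (reported 10.0%) | x = 10 (reported 20.0%) |
|---|---|---|---|
| 1 | 1/51 = 2.0% | 6/51 = 11.8% | 11/51 = 21.6% |
| 2 | 2/52 = 3.8% | 7/52 = 13.5% | 12/52 = 23.1% |
| 3 | 3/53 = 5.7% | 8/53 = 15.1% | 13/53 = 24.5% |
| 5 | 5/55 = 9.1% | 10/55 = 18.2% | 15/55 = 27.3% |

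The first omitted failure is worth 1.6 to 2.0 percentage points. With k = 0 there is no bias.

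**4. How likely is at least one such failure?**

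If the true failure rate per attempt is p, the chance of at least one in 50 attempts is 1 − (1 − p)^50. That is 64% for p = 2%, 92% for p = 5% and 99.5% for p = 10%. These rates are assumed, and a failure that occurs is not necessarily one that is omitted.

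**5. Illustration for DASH**

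Take the plan's expected mean of 13 and suppose that each omitted patient would have scored 40 (an assumption). Two omissions give (50 × 13 + 2 × 40) / 52 = 14.0; five give (50 × 13 + 5 × 40) / 55 = 15.5. The shift of 1.0 to 2.5 points is small against the 10-point minimal important change that the plan cites.

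**The case against.** The strongest reply is that the article never says that fixation must be completed, and that it expects device problems inside the cohort, since it lists "implant failure (balloon breakage)" among the complications and also collects intra-operative events. This stands. A reader might infer that every case with a balloon problem is excluded; the text does not support that. Only an attempt that ends without IlluminOss fixation is outside on the wording.

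A reader might also infer that early failures are excluded. They are not. Redisplacement, revision and severe complications are not exclusion criteria, and these patients remain eligible. Their loss is possible, not built in. The 2-week visit is the outer limit rather than the default: patients may be informed at the ED or on the ward, Table 1 places enrolment before surgery, and the visits are standard care in any case. That reduces the risk but does not remove it, because the text still permits late entry. Nor is there evidence that anyone would apply the compliance criterion with the result in mind; the point is that nothing stated prevents it.

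It may further be said that site logs belong in the full protocol. That is fair as regards the log alone, and its absence here is not the finding. The finding is the stated inclusion rule, which a log would not change. Finally, this is a declared observational series in which complications are secondary. That limits the weight of the point but does not answer it.

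**Conclusion.** The point holds as a weakness in the cohort definition. Converted attempts without IlluminOss fixation are left out by the wording, and patients with early failure may be left out through late entry. The direction favours the device. The size cannot be derived from the documents: the move from 10% to between 13.5% and 18.2% rests on an assumed 5 complications in 50 and 2 to 5 omitted failures, each counted as an event. An effect on DASH is possible and, under the assumptions shown, modest.

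It would go too far to say that complications are understated. That requires failures to occur and to be omitted, and the documents establish neither. The supported statement is that they can be understated, and that the plan as worded could not show whether they were.

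**What to change.** - Define the cohort as all consecutive, otherwise eligible patients in whom IlluminOss fixation was started, whether or not it was completed or later revised.
- Judge eligibility, including the compliance criterion, on pre-operative information only.
- Seek consent before surgery where possible. Recruitment at the ED is already allowed.
- Keep an anonymous count at each hospital of attempts, conversions and eligible patients not enrolled.
- Report procedural failure and early complications per attempted procedure, beside the results for enrolled patients.

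The cost is a change of wording and a short count at four hospitals. Using anonymous counts for patients who did not consent should be cleared with the ethics committee. As the article reports a first inclusion on August 31, 2015, attempts already made would have to be counted retrospectively from hospital records. The reported complication rates may become less favourable.
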